#### Recruitment {15}

Participant recruitment will be performed at the tertiary referral neurotological centre.

### Assignment of interventions: allocation

#### Sequence generation {16a}, concealment mechanism {16b}, and implementation {16c}

Randomized lists will be created before the beginning of the study by SPSS version 21. Then, several sealed and opaque envelopes will be made and kept securely by recognized third parties. To ensure the balance of the number of patients and age distribution between the two groups, we considered age stratification (18–35 years old and 36–65 years old) with an appropriate block size. After the patient is enrolled, the sealed envelope system will be used for the randomization of the patients into two groups. Neither the investigator nor the participants will be aware of each envelope’s contents.

### Assignment of interventions: blinding

#### Who will be blinded {17a}

Doctors and patients involved in the study will be aware of the group allocations. However, the evaluation of primary and secondary outcomes and statistical analysis will be entrusted to a third party that is not involved in the study. All patients will be identifiable with a unique study number. During the evaluation process, all members of this third party will be blind to the participant’s allocation.

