The goals of modern VS surgery are to completely remove the tumour, preserve nerve function, and reduce complications. In recent years, with the popularization and application of microscopy, continuous improvements in surgical instruments and skills, in-depth studies of the microanatomy of the cerebellopontine angle, and the application of intraoperative electrophysiological monitoring technology, the above surgical goals have largely been attained [12–15]. In addition, many factors affect the outcomes of surgery and related complications, among which the effect of different surgical positions has long been debated. Patients are easily placed in the lateral position (LP, Fig. 1B), and few complications are associated with this surgical position. However, corresponding disadvantages do exist, such as high cranial pressure, difficulty in releasing cerebrospinal fluid, unclear anatomical location, and increased requirements for assistants [5]. In contrast, the semi-sitting position (SSP, Fig. 1A) provides specific possible advantages, including drainage of blood and cerebrospinal fluid (CSF) by gravity, decreased bleeding, clean surgical field, improved surgical exposure and anatomical orientation, and ability to perform continuous bimanual dissection [5, 15–18]. However, this position carries some potential risks, such as venous air embolism (VAE) [19], tension pneumocephalus, and peripheral nerve injury [16, 20]. Despite these risks, some neurosurgeons preferred to perform posterior fossa surgeries in the SSP [15, 21]. Many studies have shown that the operational risk associated with body position is very low in the context of adequate preoperative preparation, intraoperative coordination with anaesthesiologists, and careful monitoring. Thus, SSP is safe and reliable [22–24]. [name] of Hannover, Germany, personally completed more than 4000 cases of semi-sitting VS resection. Long-term functional outcomes and surgery-related complication rates were satisfactory. Fifty patients with VSs > 4.0 cm in maximal extra-meatal diameter were reported with gross total resection, and the anatomical integrity of the facial nerve was preserved in 92% [25]. Taking all the above-mentioned advantages into consideration, SSP may lead to better surgical outcomes, such as a higher percentage of gross total resection and better facial nerve function, for patients with large VSs. However, randomized studies are required to verify this hypothesis.

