### Trial design {8}

This trial will be designed as a single-centre, open, RCT to assess the effects of different surgical positions (SSP and LP) on the surgical outcomes of large VS. The protocol was reported using the recommendations of Standard Protocol Items: Recommendations for Interventional Trials (SPIRIT) [26]. The open mode is the only possible choice for this trial because it is impossible to hide the surgical position of each patient. However, to minimize bias related to the “open” mode, the evaluation of some outcomes and the statistical analysis will be performed in a blinded fashion. The schedule of enrolment, interventions, and assessments for all study patients can be found in Fig. 3.

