**Primary outcome**		
Percentage of gross-total resection		
Extent of tumour resection	Gross total resection: total resection under the microscope, imaging without residual.	Note: The evaluation of total resection under the microscope and determination of microscopic residual tumours depend largely on subjective observations from experienced neurosurgeons according to the operation video.
	Near-total resection: microscopic residual (a few tumour capsules, < 5%), imaging no residual.	
	Subtotal resection: microscopic residual (small tumour remnant, 5–10%), imaging small tumour remnant residual.	
	Partial resection: microscopic nodular residual tumour (≥ 10%), imaging nodular residual tumour.	

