#### Adverse event reporting and harms {22}

Adverse events and postoperative complications will be assessed by the surgeon. If present, these adverse events and postoperative complications will be logged.

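### The protocol gives conflicting accounts of who rates outcomes blind, and masking of the video rating behind the primary endpoint may be imperfect

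*Protocol article*

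**What the plan says.** The protocol article describes blinding in three places.

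- *Who will be blinded {17a}*: "the evaluation of primary and secondary outcomes and statistical analysis will be entrusted to a third party that is not involved in the study". The section adds that "all members of this third party will be blind to the participant’s allocation". It names no exception. It also says that doctors and patients in the study know the allocation.
- *Trial design {8}*: the trial is open because "it is impossible to hide the surgical position of each patient". To limit the resulting bias, "the evaluation of some outcomes and the statistical analysis will be performed in a blinded fashion".
- *Adverse event reporting and harms {22}*: "Adverse events and postoperative complications will be assessed by the surgeon".

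Complications are listed as a secondary endpoint under *Outcomes {12}* and in Table 3, and the statistical methods section ({20a}) compares them between the arms.

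For the primary endpoint, Table 3 has "Gross total resection: total resection under the microscope, imaging without residual". Near-total resection is defined by a microscopic remnant below 5%, also with nothing left on imaging. A note to the table says that judging total removal and microscopic remnants will "depend largely on subjective observations from experienced neurosurgeons according to the operation video".

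The background section ({6a}) lists possible advantages of the semi-sitting position, among them "drainage of blood and cerebrospinal fluid (CSF) by gravity, decreased bleeding, clean surgical field", together with better exposure and orientation and continuous two-handed dissection.

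**The concern.** There are two separate problems.

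The first is a plain contradiction. If the surgeon assesses complications, the blinded third party does not evaluate every secondary outcome. If only some outcomes are rated blind, the unrestricted statement in {17a} is wrong. A trial report that follows {17a} would describe the safety comparison as blinded when {22} assigns it to someone who knows the position. Safety is one of the two stated aims of the trial. Some categories leave room for judgement, such as posterior cranial nerve disorders and the open rows for other events.

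The second is a risk to the primary endpoint. A blinded MRI reading cannot separate gross-total from near-total resection, because both are clear on imaging. Only the microscopic judgement separates them, and the protocol calls that judgement largely subjective. Drainage, bleeding and exposure are features an experienced neurosurgeon might recognise on video. A rater who is formally unaware of allocation could therefore guess it, and a modest shift at this one boundary would feed straight into the primary comparison.

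**Working it through.** **Contradiction.** This needs no arithmetic, only the passages side by side.

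| Section | Outcomes covered | Rater | Blind? |
|---|---|---|---|
| {17a} | all primary and secondary | third party | yes |
| {8} | some outcomes | not named | yes |
| {22} | complications (secondary) | the surgeon | no, since {17a} says doctors know the allocation |

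The third row contradicts the first, and the second is narrower than the first.

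**Which component decides the primary endpoint.** In Table 3:

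| Category | Microscope | Imaging |
|---|---|---|
| Gross total | no remnant | no residual |
| Near total | remnant below 5% | no residual |
| Subtotal | remnant 5–10% | small residual |
| Partial | remnant 10% or more | nodular residual |

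Imaging separates the first two rows from the last two. Only the microscopic and video judgement separates the first row from the second, and that is where the primary endpoint is cut.

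**The plan's own figure.** *Sample size {14}* gives 58 per group from 93% v 73%, power 80%, alpha 5% (two-sided, per {20a}) and 8% dropout.

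- Unpooled variance: n = (1.960 + 0.842)² × (0.93 × 0.07 + 0.73 × 0.27) / 0.20² = 51.5, so 52. Then 52 / 0.92 = 56.5, so 57.
- Pooled variance: 55. Then 55 / 0.92 = 59.8, so 60.

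The stated 58 lies between the two, so the sample size is not in question here. The evaluable number is 58 × 0.92 = 53.4, taken as 53 per arm.

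**Illustration of size.** The documents give no misclassification rates, so the following are assumptions:

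- true gross-total resection is equal in both arms at 83%, the midpoint of 93% and 73%;
- 53 patients per arm;
- raters move a fraction d of lateral-position gross totals to near-total, and the semi-sitting arm is rated correctly;
- the test is the uncorrected chi-square, two-sided 5%.

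The observed lateral rate is 0.83 × (1 − d). The probability of a significant result favouring semi-sitting is the sum, over all pairs of counts (x, y) that reject in that direction, of Bin(x; 53, 0.83) × Bin(y; 53, 0.83(1 − d)).

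| d | Observed semi-sitting v lateral | P(falsely finding semi-sitting better) |
|---|---|---|
| 0 | 83.0% v 83.0% | 2.5% |
| 2% | 83.0% v 81.3% | 4.1% |
| 5% | 83.0% v 78.9% | 7.8% |
| 10% | 83.0% v 74.7% | 18.3% |

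The statistical methods section also allows Fisher's exact test. With it, the first and last rows become 1.4% and 12.9%.

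**The case against.** A reader might infer that the video shows the position and that the primary rating is therefore unmasked. The documents do not support this. No section says what is in frame, and the field differences in the background section are offered only as possible advantages. The neurosurgeons who rate the video are not identified and could belong to the blinded third party. Editing or masking of clips is the kind of detail that an article leaves to the full protocol. Being able to guess the allocation is a risk to masking, not a contradiction of {17a}. This objection stands, and it limits the claim about the primary endpoint to imperfect masking.

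A reader might also take the assessor of complications to be the operating surgeon, with a bias towards the semi-sitting position. The text says only the surgeon. The intervention section ({11a}) says that both surgeons operate in both positions and have no preference. Table 3 ties haematoma to imaging and infection to cerebrospinal fluid findings, and facial function is graded by two neurologists. These points make large bias in those items less likely. They do not remove the contradiction, because an assessor who knows the allocation is still rating an outcome that {17a} describes as rated blind.

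Finally, the misclassification rates are assumed and run in one direction only. The figures show what rater drift could do, not what this trial will produce.

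**Conclusion.** The conflict between {8}, {17a} and {22} is certain and rests on the text alone. The concern about the primary endpoint holds in a limited form: its defining boundary depends on a subjective video rating that blinded imaging cannot check, and the masking of that rating may be imperfect. It is not shown to be absent.

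Under the stated assumptions, a 2% to 10% one-sided downgrade raises the chance of a false result in favour of semi-sitting from 2.5% to between about 4% and 18%, and somewhat less with Fisher's exact test. No rate in that range has a source in the protocol.

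The trial remains interpretable, but the text should be corrected before the results are reported as blinded.

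**What to change.** 1. Reconcile {8}, {17a} and {22} by stating, for each outcome, who rates it and whether that rater is blind. Say openly that masking of the video rating may be imperfect.
2. Let the surgeon log events. Have the existing third party classify the complications that can be masked (haematoma, cerebrospinal fluid leak, infection, posterior cranial nerve disorders) from imaging, laboratory data and notes with the position removed. State that venous air embolism, an intraoperative event, is not rated blind.
3. Keep the primary test unchanged. Pre-specify a supporting sensitivity analysis of residual on MRI alone (gross plus near-total v subtotal plus partial), using the 3-month scan that is already scheduled and read without position information. It is a different endpoint from the primary, so it supports interpretation and should not act as a gate on the primary claim.

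The third party and the scan are already in the plan. The cost is protocol wording, some work to de-identify notes, one extra analysis and a more modest blinding claim.

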#### Procedure for unblinding if needed {17b}

Not applicable because doctors and patients involved in the study will be aware of the group allocations.

### Data collection and management

#### Plans for assessment and collection of outcomes {18a} and data management {19}

The data in the case report form (CRF) provided by researchers should be accurate, complete, timely, and reliable. Baseline data of participants (age, sex, tumour maximum diameter, hearing level, and facial nerve function level) will be collected when they are enrolled. Independent data administrators not involved in the treatment will collect and aggregate the individual data using an online electronic data system.

#### Plans to promote participant retention and complete follow-up {18b}

The follow-up period will be at least 1 year, during which time the patients will be evaluated both clinically and radiologically. After surgery, all patients will be regularly examined at the outpatient clinic every 3–6 months. Clinical assessments, such as facial nerve function (according to the HB grading system) and hearing function (according to the AAO-HNS classification), will be performed. Postoperative MRI will be performed before discharge and 3 months after surgery. Further follow-up examinations will be performed every year. No interim analyses are planned.

#### Confidentiality {27}

The main researchers should be qualified based on the “Good Clinical Practice (GCP) training” of the State Food and Drug Administration for compliance with the training. All investigators will make every effort to ensure the safety of patient information. An independent clinical monitor within our hospital will perform an annual monitoring assessment. The main auditing procedures will include ensuring that informed consent has been obtained from all the included patients based on regulatory guidelines and verifying the content of the case report forms.

#### Plans for collection, laboratory evaluation, and storage of biological specimens for genetic or molecular analysis in this trial/future use {33}

Not applicable as no biological specimens were collected as part of this trial.

## Statistical methods

### Statistical methods for primary and secondary outcomes {20a}

All analyses will be performed using the SPSS software, version 25 (IBM Corp.) with a two-sided significance level of .05 unless otherwise stated. Continuous quantitative variables are expressed as numbers, means, standard deviations, and medians. Comparisons between proportions for the categorical variables will be performed using the chi-square test, Fisher’s exact test, or Mann-Whitney *U* test. In addition, Student’s *t* test and non-parametric analysis will be used for continuous variables with and without normal distributions. Differences in the percentage of gross total resection, facial nerve function, hearing function, general complications, and special complications between the SSP and LP groups will be evaluated using Fisher’s exact test or chi-squared test. Differences in the surgical positioning time, time of operation, hospital stay, and total hospitalization fee between the SSP and LP groups will be evaluated using Student’s *t* test or Mann-Whitney *U* test. Regression analysis will be used to evaluate the influence of SSP versus LP, tumour size, and surgeons on the percentage of gross total resection, as well as SSP versus LP, tumour size, surgeons, and the percentage of gross total resection on facial nerve function and hearing function. Association of the time of operation with SSP versus LP, tumour size, the percentage of gross total resection, and surgeons will be evaluated using ANOVA. If the patient has a PFO, he or she will not be excluded from the study but analysed according to the SSP group they were originally assigned after the LP surgery.

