**Inclusion criteria**	
Age between 18 and 65 years old, regardless of gender	
Preoperative imaging diagnosis of VS, Koos grade 4	
Preoperative American Society of Anaesthesiologists (ASA) score 1–2 [27, 28]	
Preoperative evaluation of facial nerve function for House-Brackmann (HB) grading system I level [29]	

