**Secondary outcomes**		
Facial nerve function	As one of the inclusion criteria, facial nerve function was documented photographically at rest and while performing standardized facial expressions at defined time points (preoperatively, discharge, and 6 and 12 months after surgery).	This feature was evaluated by two experienced neurologists and classified according to the HB grading system [29].
Hearing function	Hearing level will be analysed and evaluated using pure-tone audiometry (PTA) and speech discrimination score (SDS) according to the guidelines of the American Association of Otolaryngology–Head and Neck Surgery (AAO-HNS) classification [30].	Serviceable hearing was defined as either class A (PTA ≤ 30 dB, SDS ≥ 70%) or class B (30 < PTA ≤ 50 dB, SDS ≥ 50%) and non-serviceable hearing as class C (PTA > 50 dB, SDS ≥ 50%) or class D (any PTA, SDS < 50%).
Surgical positioning time		
Time of operation	Craniotomy time	
	Intradural microsurgery time	
	Scalp closure surgery time	
Hospital stay		
Total hospitalization fee		
General complications	Intracranial haematoma: head imaging examination will be performed within 3 h after surgery.	
	Cerebrospinal fluid leakage (incision leakage or nasal leakage).	
	Intracranial infection: postoperative fever, cerebrospinal fluid routine, and biochemical evidence of infection.	
	Cranial nerve disorders in the posterior group: drinking water choking cough, articulation disorder, etc.	
	Others	
Special complications	VAE	
	Others	
Recurrence		

*HB* House-Brackmann, *VAE* Venous air embolism

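### Facial nerve function is an ordered grade with no stated cut-point, but the sentence that names its test offers only Fisher's exact or chi-squared, which do not use the order

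*Protocol article*

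**What the plan says.** Table 3 puts facial nerve function first among the secondary outcomes, assessed before surgery, at discharge, and at 6 and 12 months. It adds: "This feature was evaluated by two experienced neurologists and classified according to the HB grading system". No cut-point on the HB grade appears there or elsewhere in the article. Hearing, in the same table, does get one: "Serviceable hearing was defined as either class A" or class B, with classes C and D counted as non-serviceable. Table 2 requires grade I at entry: "Preoperative evaluation of facial nerve function for House-Brackmann (HB) grading system I level".

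Section {20a} then makes three statements that bear on the analysis.

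- In general: "Comparisons between proportions for the categorical variables will be performed using the chi-square test, Fisher’s exact test, or Mann-Whitney" U.
- By outcome: "Differences in the percentage of gross total resection, facial nerve function, hearing function, general complications, and special complications between the SSP and LP groups" are assigned to Fisher's exact or chi-squared test. The next sentence offers Mann-Whitney U by name, but only for positioning time, operation time, hospital stay and fee.
- A regression of facial nerve function on position, tumour size, surgeon and gross total resection. The type of model is not named.

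The background section gives the hypothesis: the semi-sitting position (SSP) may lead to more gross total resections and better facial nerve function than the lateral position (LP).

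**The concern.** The hypothesis for facial function has a direction, and the outcome has an order. A chi-squared or Fisher test on the full grade table uses neither. It asks only whether the two distributions differ, and it gives the same p-value if the grade labels are shuffled. A significant result need not mean that either position is better, and a moderate shift towards better grades is easy to miss. Because every patient enters at grade I, the postoperative grade can be read directly as an ordered outcome.

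If a split of the grades is intended instead, the direction is clear but information is lost. The cut-point is also not fixed, so it could be chosen after the data are seen.

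The two sentences in {20a} do not agree on whether a rank test is available for this outcome. The regression does not settle it. Gross total resection is determined after randomisation and is the very outcome that position is expected to change. A position effect adjusted for it is not the total effect of position on facial function.

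**Working it through.** **The plan's own figure.** Section {14} gives 93% v 73%, 80% power, 5% alpha, 8% dropout and 58 per group.

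- Pooled variance, two-sided: n = [1.96·√(2·0.83·0.17) + 0.8416·√(0.93·0.07 + 0.73·0.27)]² / 0.20² = (1.041 + 0.431)² / 0.04 ≈ 54.2, so 55. Then 55/0.92 = 59.8, so 60.
- Unpooled variance: (1.96 + 0.8416)²·0.2622/0.04 ≈ 51.5, so 52. Then 52/0.92 = 56.5, so 57.

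The stated 58 lies between these, so it is reproduced closely. Evaluable per arm: 58 × 0.92 = 53.4, taken as 53. The article states no power for facial nerve function.

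**Assumptions.** The article gives no HB distribution, no effect size and no number of grades. Four LP distributions over six grades (in %) were assumed:

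- A: 30/25/20/12/8/5
- B: 50/20/15/8/5/2
- C: equal in all six
- D: 15/20/25/20/12/8

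The SSP distribution comes from a proportional-odds shift: each cumulative odds c/(1−c) is multiplied by the odds ratio (OR). For A at OR 2.5, 0.30/0.70 × 2.5 = 1.071, so P(grade I) = 1.071/2.071 = 0.517. The full SSP distribution is then 51.7/23.6/12.9/6.1/3.6/2.1.

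**Simulated power.** 3,000 trials per scenario, 53 per arm, two-sided 5%. Ranges run over A to D.

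| OR | Chi-squared, full table | Mann-Whitney | I–II v III+, chi-squared | I–II v III+, Fisher |
|---|---|---|---|---|
| 1.0 | 4–5% | 5–6% | 4–6% | 2–3% |
| 2.0 | 21–28% | 44–52% | 33–42% | 26–35% |
| 2.5 | 37–47% | 67–75% | 50–63% | 41–56% |
| 3.0 | 52–66% | 79–89% | 62–78% | 52–72% |

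Hand check of one split cell (A, OR 2.5). Grades I–II are 55% v 51.7 + 23.6 = 75.3%, a difference of 0.203 with mean 0.652. The null SE is √(2·0.652·0.348/53) = 0.0925 and the alternative SE is √((0.55·0.45 + 0.753·0.247)/53) = 0.0904. Then (0.203 − 1.96·0.0925)/0.0904 ≈ 0.24, a power of about 60%. The simulation gave 60.4%.

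**Loss against Mann-Whitney, within each distribution, OR 2.0 to 3.0.**

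- Full-table chi-squared: about 23 to 30 points (for example A at OR 2.5: 72.2 − 44.5 = 27.7).
- I–II v III+ by chi-squared: about 8 to 18 points (A at OR 2.0: 50.1 − 41.7 = 8.4; B at OR 3.0: 79.1 − 61.5 = 17.6).
- I–II v III+ by Fisher: about 16 to 27 points.

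**Fewer occupied grades** (OR 2.5, 53 per arm, 4,000 trials).

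- Four grades (35/30/20/15): 54.0% v 70.9%, a loss of about 17 points.
- Three grades (40/35/25): 57.8% v 68.0%, a loss of about 10 points.

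**Sample size equivalent** (A, OR 2.5). About 80% power needs about 64 per arm with Mann-Whitney and about 105 with the full-table chi-squared.

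**When the shift is not consistent.** Take LP as A and SSP as 30/25/38/5/2/0, a benefit confined to the worse grades. Chi-squared then has 58% power and Mann-Whitney 13%. With SSP at 15/40/30/12/3/0, where some grades gain and others lose, the figures are 62% and 6%.

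**The case against.** A reader might infer that the protocol fixes a six-column chi-squared test. It does not. Facial nerve function stands in a sentence with outcomes that are proportions or have a defined split, so a proportion with good function is a natural reading. On that reading the test shows which position did better, and the loss falls to about 8–18 points with chi-squared. This stands. But no HB split is defined, although Table 3 defines one for hearing, and a loss remains.

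A rank test is already in the general list for categorical variables, where it makes sense only for ordered categories. This also stands in part: the two sentences need reconciling, and the plan does not exclude a rank test outright. Yet the sentence that names the outcome omits it, and the more specific sentence would ordinarily govern.

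A reader might also infer that the plan gives no direction of effect at all. That goes too far, since the planned regression would give a signed position coefficient. That coefficient is, however, conditional on gross total resection, and no ordinal model is named.

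The power figures rest on assumed distributions and on a proportional-odds shift, the setting that suits Mann-Whitney. The reversal is not limited to effects without a direction: in one scenario above, a benefit confined to the worse grades was found far more often by chi-squared. This stands as a limit on the size of the loss.

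**Conclusion.** The point holds as a poorly fixed analysis of a secondary endpoint. The test named for facial nerve function either ignores the order of the grades or relies on a cut-point that the article does not state, and it sits uneasily with the general sentence in the same section.

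Under a consistent shift with 53 evaluable per arm and OR 2.5, the loss against a rank test is about 27–30 points with six grades, about 17 with four and about 10 with three. For a I–II v III+ chi-squared it is about 8–18 points over ORs of 2.0 to 3.0. These sizes depend on assumed distributions and can reverse if position does not move grades consistently.

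Type I error and the gross total resection analysis are not affected. Two further inferences are not supported. The article does not call facial function a key endpoint: it is listed first among the secondary endpoints and named in the hypothesis, and the trial is powered on resection alone. Nor does the argument carry over to hearing, for which Table 3 defines serviceable v non-serviceable and Table 2 sets no baseline level.

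**What to change.** Reconcile the two sentences in {20a} by taking facial nerve function out of the Fisher or chi-squared list and naming its analysis. Compare HB grade at 12 months, a time point already in Table 3, with Mann-Whitney U or a proportional-odds model. The model would include position, tumour diameter, surgeon and the age stratum used in randomisation, but not gross total resection. Report a common odds ratio with its confidence interval, and keep I–II v III–VI as a descriptive summary. Leave hearing on its defined split.

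The cost is a change of wording, with no new data or patients. The small downside is reliance on a consistent shift along the scale, to be checked through the proportional-odds assumption.

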### Outcomes {12}

The primary endpoint will be the percentage of gross total resection. The secondary endpoints will include facial nerve function, hearing preservation, surgical position placement time, time of operation (skin-to-skin surgical time), hospital stay, total hospitalization fee, and complications. The details of the primary and secondary outcomes are provided in Table 3.

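### The hearing endpoint is named preservation, but the planned hearing analyses leave out the baseline hearing that the trial collects

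*Protocol article*

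**What the plan says.** The Outcomes section {12} states: "The secondary endpoints will include facial nerve function, hearing preservation", followed by the remaining secondary endpoints. The Abstract uses the same name for the hearing endpoint.

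Table 3 calls the item hearing function and grades it by pure-tone audiometry (PTA) and speech discrimination score (SDS) into AAO-HNS classes. It draws a line between serviceable and non-serviceable hearing: "Serviceable hearing was defined as either class A" or class B, with C and D non-serviceable. It does not say how that line turns into preservation.

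The section on statistical methods {20a} gives two hearing analyses:
- A between-arm test: differences in "facial nerve function, hearing function, general complications, and special complications between the SSP and LP groups will be evaluated using" Fisher's exact or chi-squared test. No subset is named for hearing.
- A regression, with these terms: "SSP versus LP, tumour size, surgeons, and the percentage of gross total resection on facial nerve function and hearing function".

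The data collection section {18a} and {19} states: "Baseline data of participants (age, sex, tumour maximum diameter, hearing level, and facial nerve function level) will be collected when they are enrolled".

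Table 2 requires House-Brackmann grade I facial function at entry and sets no hearing criterion. Randomization is stratified by age only. The section on additional analyses {20b} adds nothing and refers back to {20a}.

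**The concern.** Preservation is a statement about change: the patient had serviceable hearing before surgery and still has it afterwards. The planned analyses look only at hearing after surgery. For facial function this does no harm, because everyone enters at the same grade. For hearing the entry level can run from class A to class D, and the listed terms do not account for it.

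A patient who enters at class C or D cannot preserve serviceable hearing under either position. If the outcome is serviceable hearing and such patients are in the denominator, they count as failures in both arms and shrink the difference between them. Entry hearing is also a plausible strong predictor of later hearing, so leaving it out of the regression gives up precision. The reader then gets a comparison of postoperative hearing levels, not an answer to whether one position preserves hearing more often.

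**Working it through.** **Plan figures.** The protocol states no rate, difference or power for hearing, so there is no hearing figure to reproduce. The only plan inputs used are 58 per group, 8% loss and two-sided alpha 0.05. Evaluable patients per arm: 58 × (1 − 0.08) = 53.4, taken as 53.

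**Assumptions (not in the documents).** Share s with class A or B before surgery: 20–50%. Preservation among them, semi-sitting v lateral: 60% v 30%, and a smaller contrast of 50% v 30%. The outcome is serviceable hearing, yes or no.

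**Dilution.** With everyone in the denominator, each arm's rate is s × its preservation rate, so the difference is s × (pS − pL).
- 60% v 30%: 0.2 × 30 = 6 points, up to 0.5 × 30 = 15 points.
- 50% v 30%: 0.2 × 20 = 4 points, up to 0.5 × 20 = 10 points.
- Restricted to serviceable hearing at entry, the difference stays at 30 or 20 points, with about 53 × 0.2 = 11 to 53 × 0.5 = 27 patients per arm.

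**Power, one case by formula.** Power = Φ[(d − 1.96 × SE0) / SE1], with SE0 from the pooled rate and SE1 from the separate rates. Take s = 30% and 60% v 30%:
- Everyone: rates 0.18 and 0.09, d = 0.09, n = 53, SE0 = 0.0664, SE1 = 0.0658. Power = Φ[(0.09 − 0.1301)/0.0658] = 27%.
- Restricted: rates 0.60 and 0.30, d = 0.30, n = 15.9, SE0 = 0.1764, SE1 = 0.1682. Power = Φ[(0.30 − 0.3458)/0.1682] = 39%.

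**Power by simulation.** Uncorrected chi-squared test, with the number serviceable at entry drawn at random in each arm:

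| Share serviceable at entry | 60% v 30%: everyone | 60% v 30%: restricted | 50% v 30%: everyone | 50% v 30%: restricted |
|---|---|---|---|---|
| 20% | 18% | 29% | 11% | 16% |
| 30% | 27% | 41% | 15% | 21% |
| 40% | 37% | 51% | 20% | 27% |
| 50% | 47% | 61% | 25% | 32% |

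The restricted comparison does better in every row despite fewer patients. With Fisher's exact test, the other test the protocol names, power is lower but the order is the same: 10–37% v 20–53% at 60% v 30%, and 5–19% v 10–26% at 50% v 30%.

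**Chance imbalance.** Over the same range of s, the simulated chance that the arms differ by at least 10 points in the share serviceable at entry is 18–29%. With 40% preservation in both arms, a 10-point imbalance moves the all-patient outcome by 0.10 × 40 = 4 points.

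**The case against.** Four points can be made for the plan, and each limits the finding.

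- **The denominator is not stated.** A reader might infer that the plan commits to testing hearing in every randomized patient. It does not say so; it names no subset. The endpoint's name, the definition of serviceable hearing and the recorded baseline are together what an at-risk analysis needs, and a full protocol or analysis plan may supply it. This stands. What remains is that the published text gives the endpoint two names and spells out the regression terms without baseline hearing.
- **Class C and D do not mean that nothing can be lost.** Table 3 puts class C at SDS of 50% or more, so such a patient can still fall to class D, and class D is not defined as deafness. If the four classes were compared, these patients would contribute and the dilution arithmetic would not apply. This stands: dilution is conditional on a serviceable yes/no outcome, which section {20a} does not fix.
- **Randomization deals with imbalance.** A reader might infer that a chance difference in entry hearing would bias the comparison. It would not in expectation, and the unadjusted test's error rate already allows for such differences. This stands. Adjustment is a matter of precision, and its absence is not an error in a randomized comparison.
- **The size is assumed.** No hearing rate is in the document, and at 50% v 30% the gain is only about 5 to 7 points of power. This stands too, although the direction was the same in every scenario run.

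**Conclusion.** The point holds in a limited form. The endpoint is called preservation, but the hearing analyses as written do not use the baseline hearing class on which preservation depends. The regression omission is explicit, because its terms are listed. The plan therefore loses precision, its result does not directly estimate preservation and, if serviceable hearing is the outcome, the effect shrinks in proportion to the share serviceable at entry.

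Under the assumptions shown, restricting to patients with serviceable hearing at entry raises power by about 11–15 points at 60% v 30% and about 5–7 points at 50% v 30%. No scenario reaches 80%, so the repair makes the question clearer without making hearing confirmatory. The protocol claims no power for hearing. The primary endpoint, its test and the sample size of 116 are untouched. The change is worth making because it is nearly free, not because the planned comparison is invalid.

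**What to change.** In the section on statistical methods {20a}:
1. Add baseline hearing class, or baseline PTA and SDS, as a covariate in the hearing regression.
2. Define hearing preservation as class A or B at 12 months among patients with class A or B before surgery, and compare it between the arms as randomized. The subset is defined before surgery, so the randomized comparison within it remains valid.
3. Use the same endpoint name in the Abstract, Outcomes {12}, Table 3 and section {20a}.

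The cost is wording only. Baseline hearing is already collected and 12 months is already a planned follow-up point, so no extra patients or visits are needed. The drawback is a smaller denominator for the preservation comparison, about 11 to 27 per arm under the assumed shares. The definition should be fixed before hearing outcomes are analysed, so that the choice of denominator cannot depend on the results.
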